**Figure 1. f1:**
[figure not shown]
Study flow diagram.

Verbal autopsy – The follow up team will inform the verbal autopsy (VA) team regarding any perinatal/neonatal death among the enrolled participants. The VA team will visit the family after the grieving period (at least 14 days after the death). VA will be performed on a
structured questionnaire.

Withdrawal and early termination – The participant may voluntarily withdraw from the study for any reason at any time. The investigator may also withdraw mother or baby from the study in order to protect their safety if, in their opinion, continuing participation would jeopardize the participants health. Any participant withdrawal or early termination will be documented in the appropriate study forms

Training and quality control – The physician sonographer has voluntarily started her training under the supervision of a trained fetal echocardiographer at AKU for the past 6–8 weeks. This training will continue for another 6 weeks followed by one week observation of her skills at the PHC to perform fetal Dopplers. During the project duration, 10–15% of her images will be monitored every week (by 2 trained fetal echocardiographers) to ensure the quality and correct acquisition of the required images. Retraining will be offered if required.

Data transfer and analysis – Fetal echo and ultrasound data will be interpreted jointly by the research team in a joint analysis meeting at AKU and Universitat Pompeu Fabra (UPF). Analysis will include developing the machine learning algorithm required to predict adverse perinatal outcomes. To fuse and order multivariate heterogeneous data, and be agnostic of any outcome, the Multiple Kernel Learning (MKL) methodology will be utilized in a non-supervised setting. The data would undergo non-linear dimensionality reduction to extract the most discriminate features from the multiple and rich input variables allowing for independent complex interrelation with abnormalities. Identifying clusters of individuals, after identifying the most relevant discriminate patterns in the population, and relating this to clinical findings and outcome, subsequently allows for the identification of phenogroups with similar outcome. When data from a new individual, not used for the learning phase, is available, the most similar patients from the learning phase can be identified (by projection of input data into the learned low-dimensional space) and the pheno-group membership can be quantified from which predicted outcome can be derived assuming it will be similar to the expected outcome of the group (refer to
Figure 2).

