## Abstract

**Background:** In Pakistan, stillbirth rates and early neonatal mortality rates are amongst the highest in the world. The aim of this study is to provide proof of concept for using a computational model of fetal haemodynamics, combined with machine learning. This model will be based on Doppler patterns of the fetal cardiovascular, cerebral and placental flows with the goal to identify those fetuses at increased risk of adverse perinatal outcomes such as stillbirth, perinatal mortality and other neonatal morbidities.

**Methods:** This will be prospective one group cohort study which will be conducted in Ibrahim Hyderi, a peri-urban settlement in south east of Karachi. The eligibility criteria include pregnant women between 22-34 weeks who reside in the study area. Once enrolled, in addition to the performing fetal ultrasound to obtain Dopplers, data on socio-demographic, maternal anthropometry, haemoglobin and cardiotocography will be obtained on the pregnant women.

**Discussion:** The machine learning approach for predicting adverse perinatal outcomes obtained from the current study will be validated in a larger population at the next stage. The data will allow for early interventions to improve perinatal outcomes.

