^11^. The results also suggested that patient specific haemodynamic parameters estimated with the computational model had the advantage of studying the effects of individual flow changes across the fetus and placenta which cannot be assessed in a clinical setting
^7^. This would help in understanding the pathophysiology of disease states in a more comprehensive manner and suggest possible interventions.

The Doppler flow allows us to assess the fetus that is at risk irrespective of the gestational age. It will also allow us to identify at-risk fetus without relying on anthropometric measures. As long as we are able to able to obtain the Doppler patterns on the fetus we will be able to determine if the patterns are normal or abnormal, with less of a concern of determining an accurate gestational age. In addition to obtaining fetal Dopplers, one echocardiogram will be performed on the mother. The echocardiogram will look at the four chamber view of the heart in the mother. This data may help us identify maternal etiology for poor perinatal outcomes and thus provides insights into intervention.

Though UmbiFlow (jointly developed by Medical Research Council (MRC) Unit for Perinatal Mortality, the MRC and the Centre for Scientific and Industrial Research (CSIR) South Africa), a portable device used to detect IUGR by assessing continuous wave Doppler blood flow across the placental end of the umbilical artery reported reduced number of unnecessary referrals to a higher level health facility in cases suspected of IUGR
^8^, it studies waveform across one arterial bed while our model takes into account 6 arterial beds which play a critical role in the fetal circulation.

The aim of this study is to obtain proof of concept for using a computational model of fetal hemodynamics, combined with machine learning based on Doppler patterns of the fetal cardiovascular, cerebral and placental flows, to identify those at increased risk of adverse perinatal outcomes such as stillbirth, perinatal mortality, and other neonatal morbidities. We will also compare the sensitivity and specificity of UmbiFlow with the machine learning model in predicting adverse perinatal outcomes.

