Sample size estimation – The sample size is based on outcomes of the pregnancies and not based on etiology of outcome. For the training of the machine learning, as much data as possible is required and this would be typically in the order of magnitude of thousands of patients. Given that this is not feasible in the pilot study, the training data will be mainly synthetically generated through a computational model of the fetal circulation. This allows the generation of thousands of 'individuals'. A recent randomized clinical trial conducted on machine learning in heart failure with 1106 patients with 20% having an adverse primary outcome and 5 different phenotypes, it was seen that above a sample size of 500 patients, the learned information becomes stable and doesn't change much
^10^. Additionally, we will be using socio-demographic, and pregnancy and labor characteristics, along with the Doppler, where the combined analysis should make the detection additionally more robust.

In the study area there are 30 stillbirths per 1000 total births while there are 30 neonatal deaths per 1000 live births. If 500 pregnant women are to be enrolled in the study duration, we expect to find approximately 25–30 adverse perinatal outcomes. To account for loss to follow up, we will inflate the sample size by 5% and enroll 525 pregnant women. Sample size was estimated from experience with the proposed machine learning approach, where stability of the learning phase was reached around 500 included patients
^18^, combined with the fact that data augmentation of the training set will be performed using the previously validated computational model of the fetal circulation
^7^.

Recruitment – Household surveillance will be done by community health workers (CHWs) in the catchment area in a sequential manner to identify pregnant women. Eligible women between 22–34 weeks of gestation on last menstrual period (LMP) will then have the purpose of the study explained to them and be invited for an ultrasound scan. At the clinic, all inclusion/exclusion criteria will be assessed. All screening procedures will be documented in the appropriate study forms, including logs and case report forms. Clinical assessments and findings will also be documented as appropriate. No identifying information will be retained for women who do not enroll in the study.

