## Discussion

The study will start recruitment in March 2018. Training the machine learning algorithms with data generated from the computational model and validating it in a population at risk would enable to identify the fetus and placenta that maybe compromised and be at risk for higher perinatal morbidity and mortality. This data would allow screening of pregnant women to detect at- risk and high-risk pregnancies. Early detection of these pregnancies would allow for timely referral to improve outcomes. Please refer to
Figure 3 for the clinical decision making algorithm that may be proposed.

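### The protocol does not settle whether the enrolled women train or test the model, and the UmbiFlow comparison names no evaluation sample, so the model's accuracy could be flattered

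*Protocol article*

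**What the plan says.** Several parts of the protocol article bear on which data build the model and which data test it.

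- **Introduction, aim:** "We will also compare the sensitivity and specificity of UmbiFlow with the machine learning model in predicting adverse perinatal outcomes". No evaluation sample is named.
- **Sample size estimation:** the training data are to be mainly synthetic, from a computational model of the fetal circulation. The cohort size is nevertheless justified because "stability of the learning phase was reached around 500 included patients", with the synthetic data described as augmenting the training set.
- **Second visit:** every scan of a woman, one or two, goes into the model. UmbiFlow is recorded only at this visit, at 30–34 weeks.
- **Data transfer and analysis:** multiple kernel learning is run unsupervised and without regard to outcome. Phenogroups then come from "Identifying clusters of individuals, after identifying the most relevant discriminate patterns in the population, and relating this to clinical findings and outcome". A further sentence explains how a person outside the learning phase would be projected into the learned space and given the expected outcome of her group.
- **Discussion:** "Training the machine learning algorithms with data generated from the computational model and validating it in a population at risk".
- **Abstract:** the approach obtained from this study "will be validated in a larger population at the next stage".

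**The concern.** The same cohort appears as a learning sample, as a possible validation sample, and as a forerunner to a later validation. The first and third roles fit together; the second does not fit easily with them.

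This matters because of the UmbiFlow comparison. A phenogroup predicts nothing until an outcome rate is attached to it, and the only outcomes the article describes are those followed up in the enrolled women. UmbiFlow readings also exist only in these women. If group risks are estimated in them and sensitivity and specificity are then counted in them, each event helps to label its own group as high risk and is then scored as correctly detected. An UmbiFlow cut-off fixed beforehand gains no such advantage.

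The study is a proof of concept meant to lead to screening and referral, so a comparison tilted toward the model could support moving on when little or no real discrimination exists.

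**Working it through.** **1. The plan's own figures.** The inputs are "In the study area there are 30 stillbirths per 1000 total births while there are 30 neonatal deaths per 1000 live births" and 500 women.

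- Stillbirths: 500 × 0.03 = 15.
- Neonatal deaths: (500 − 15) × 0.03 = 14.55.
- Total: 29.55, which agrees with "If 500 pregnant women are to be enrolled in the study duration, we expect to find approximately 25–30 adverse perinatal outcomes".
- The primary outcome counts deaths in the first 7 days only. If 65–85% of neonatal deaths fall there (an assumption), the total is 15 + 14.55 × 0.65 = 24.5 to 15 + 14.55 × 0.85 = 27.4.
- Enrolment: 500 × 1.05 = 525, as stated.

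The article gives no accuracy, power or optimism figure, so there is none to reproduce.

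**2. The roles side by side.**

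| Section | Role of the enrolled women |
|---|---|
| Sample size estimation | Learning sample, augmented by synthetic data |
| Second visit | All scans enter the model |
| Data transfer and analysis | Clusters related to outcome; no women reserved |
| Discussion | Possibly the population in which a synthetically trained model is validated |
| Abstract | Source of the approach; validation comes later |
| Introduction | Only women with UmbiFlow data, hence the comparison sample |

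**3. Size of the bias if labelling and scoring share the same women.** Suppose K groups of equal size have no relation to outcome, and groups with an above-average event rate are called high risk. With N women and E events, the apparent Youden index (sensitivity + specificity − 1) is half the sum over groups of the absolute difference between the group's share of events and its share of non-events. Its expected value is approximately

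J ≈ (K/2) × 0.798 × [N / (E(N − E))] × √[E × (1/K)(1 − 1/K) × (N − E)/(N − 1)],

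where 0.798 is the mean absolute value of a standard normal variable.

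With N = 500 and E = 28, N/(E(N − E)) = 500/(28 × 472) = 0.0378, and (N − E)/(N − 1) = 472/499 = 0.946.

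- K = 5: √(28 × 0.16 × 0.946) = 2.06; J ≈ 2.5 × 0.798 × 0.0378 × 2.06 = 0.155.
- K = 10: √(28 × 0.09 × 0.946) = 1.54; J ≈ 5 × 0.798 × 0.0378 × 1.54 = 0.23.

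A simulation of the same set-up (N = 500, random groups, 25 or 30 events) agrees:

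| Groups | Apparent Youden index, same women | Youden index, new women |
|---|---|---|
| 2 | 0.08 | 0.00 |
| 5 | 0.15–0.16 | 0.00 |
| 10 | 0.22–0.25 | 0.00 |
| 20 | 0.33–0.36 | 0.00 |

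A second simulation clustered five independent noise inputs by k-means, with 28 events, and scored each woman by her cluster's event rate. The in-sample AUC was 0.60 with 5 clusters and 0.65 with 10, against 0.50 in new women.

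**4. Precision.** With 25–30 events, a sensitivity near 70% has an exact 95% interval of 0.51–0.88 (18/25) or 0.51–0.85 (21/30). Honest estimates will therefore be wide as well as lower.

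**The case against.** A reader might infer that the protocol plans to score the model in the women it learned from. The documents do not say so.

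- The training data are to be mainly synthetic.
- The embedding and clusters ignore outcome, so they are not fitted to it. Bias can enter only where groups are linked to outcome, or where the number of groups or the cut-off is chosen.
- The analysis section describes projecting individuals who were not used for learning. That is the mechanism cross-validation would need, so in-sample scoring is not the only possibility.
- A full analysis plan, not shown, may specify cross-validation. Its absence from an article proves nothing.
- Learning now and validating in a larger population later is a coherent sequence, and the Discussion does not say that its population at risk is this cohort.

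A reader might also score each woman by her 20 most similar patients with herself included, which gives an AUC of 0.75 on pure noise. That figure is set aside, because the article describes the similar-patient step only for people outside the learning phase. Nor is the comparison made in all 500 or 525 women: only those with a 30–34 week scan have UmbiFlow data.

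These points stand, and they make the bias conditional. They do not remove the inconsistency. No passage says that the circulation model generates perinatal outcomes, so synthetic training data do not supply the group risks. The new-individual sentence reserves no women from this cohort. The UmbiFlow comparison belongs to this study and cannot be left to the later one.

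**Conclusion.** The concern holds as an inconsistency with a conditional consequence. The sample size, second visit and analysis sections treat the enrolled women as the learning sample that supplies phenogroup outcome rates. The Discussion suggests validation after synthetic training, the Abstract postpones validation, and the UmbiFlow comparison has no stated evaluation sample.

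If group risks, number of groups or cut-off come from the outcomes of the women in whom accuracy is computed, the model gains an apparent Youden index of about 0.15 (5 groups) to 0.23 (10 groups), or an AUC of about 0.60 to 0.65, with no real signal.

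These sizes rest on assumptions:

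- The number of groups and the inputs are not given in the article, and the illustrations use neither multiple kernel learning nor synthetic data.
- The endpoint is taken as the 25–30 deaths. A wider endpoint that includes common morbidities would have more events and less optimism; restriction to women with a second-visit scan would leave fewer events and more.
- UmbiFlow is taken to have a cut-off fixed beforehand, which the article does not state.

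The article sets no success threshold, so it cannot be said that a false proof of concept would be declared.

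**What to change.** 1. State one role for the enrolled women, and bring the Abstract, the sample size section and the Discussion into line with it.
2. Take the model's sensitivity, specificity and AUC from one of two sources:
   - out-of-fold predictions from stratified cross-validation, split by woman because she may contribute two scans, with the embedding, number of groups, phenogroup risks and cut-off re-derived in each training fold; or
   - a model, including its risk labels and cut-off, frozen before outcomes are linked.
3. Compare these predictions with UmbiFlow at a pre-specified cut-off, in the women who have a 30–34 week scan.
4. If neither source is used, label the comparison as apparent (in-sample) accuracy and do not call it validation.

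The cost is wording and computing time, with no new data collection. The reported accuracy will probably be lower and its intervals wider.

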**Figure 2. f2:**
[figure not shown]
Machine learning algorithm for this study.

Statistical analysis – Classical data analysis will be performed using
SPSS version 20.0. Data will be reported as percentages and means +/- standard deviation where appropriate. Pearson chi-square will be used to compare qualitative data between groups. A student's t-test or Mann Whitney U test (based on assumption of normality) will be used to compare data between groups with presence or absence of adverse perinatal outcomes. Associations between various Doppler and model-based parameters and adverse perinatal outcome will be analyzed by multiple logistic regression. Machine learning will be performed using the Multiple Kernel Learning approach developed in-house and described previously
^18^.

Ethical concerns – This study has been approved by AKU Ethics Review Committee (4872-Ped-ERC-17). Written informed consent will be obtained from each pregnant woman to ensure that the she is informed of and fully understands what will and may happen to her and her baby while participating in the research study. If the woman requests for additional time or indicates the need for consultation with other family members, she will be provided time, as long as she remains in the studies window period. Informed consent will be obtained by the research assistant at the center before any kind of study data is obtained. Fetal ultrasonography will require additional 15–20 minutes which may cause the woman some inconvenience. This will be clearly explained prior to recruitment. The patient will also hold the right of requesting discontinuation of scan. For any abnormal finding on fetal ultrasound or pregnancy related complication, the woman will be examined by the PHC physician. If there is need for hospital referral, facilitated referral will be done to the pregnant woman’s hospital of choice, which usually is Jinnah Postgraduate Medical Center which is a public tertiary level health center in Karachi. There will be no additional cost to the family for participation in this project.

The results of this study will be shared through newspaper articles in the local media, continuous medical education seminars, conference proceedings and publications in well reputed journals.

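### Student's t-test is chosen on normality alone, although the death outcomes imply a split of about 17:1, at which the equal-variance test is miscalibrated if the groups differ in spread (minor)

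*Protocol article*

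**What the plan says.** The Statistical analysis paragraph of the protocol article plans a Student's "t-test or Mann Whitney U test (based on assumption of normality) will be used to compare data between groups", and defines these as "groups with presence or absence of adverse perinatal outcomes". Normality is the only stated basis for choosing between the two tests. The paragraph does not mention equal or unequal variances.

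The size of the two groups can be inferred from the Sample size estimation paragraph. It gives local rates of "30 stillbirths per 1000 total births while there are 30 neonatal deaths per 1000 live births" and says of 500 women that "we expect to find approximately 25–30 adverse perinatal outcomes". It adds that "The sample size is based on outcomes of the pregnancies and not based on etiology of outcome", so the adverse group is mixed as to cause.

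Two other parts of the analysis bear on the weight of the point. The sentence after the t-test assigns the associations of Doppler and model-based parameters with adverse outcome to multiple logistic regression. The study's main aim rests on the Multiple Kernel Learning model.

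**The concern.** In ordinary usage Student's two-sample t-test is the equal-variance test: it pools the two SDs. With about 28 women in one group and 472 in the other, the pooled SD is almost wholly that of the large group, while the true standard error of the difference is driven by the small group. If the small group is more variable, the computed standard error is too small and p-values and intervals look too precise. If it is less variable, the standard error is too large and power is lost.

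The groups are formed by outcome, not by randomisation, so nothing makes their variances equal. The adverse group is also taken regardless of cause, and the Introduction links absent or reversed flow to poor outcome. Some adverse cases could therefore have strongly abnormal flow while others look normal, which would widen that group's spread. At stake is the calibration of the unadjusted comparisons.

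**Working it through.** **Inputs from the protocol article (Sample size estimation).** 500 women for analysis; 30 stillbirths per 1000 total births; 30 neonatal deaths per 1000 live births; 25–30 expected adverse outcomes; 525 enrolled to allow for 5% loss.

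**Assumptions.** The documents give no SD and no significance level for these tests. The ratio r = SD(adverse)/SD(other) is varied, the level is two-sided 5%, and data are normal unless stated otherwise.

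**Step 1: the plan's own figure.** Stillbirths: 500 × 0.030 = 15. Neonatal deaths: 485 × 0.030 = 14.55. The sum is 29.55, inside the stated 25–30. The lower end fits if about 10/14.55 = 69% of neonatal deaths are early. After 5% loss, 525 × 0.95 ≈ 499, so 500 is a fair analysis size. The splits are 25/475 (19:1), 28/472 (16.9:1) and 30/470 (15.7:1).

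**Step 2: equal means, unequal spread, 28 against 472.**

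- Pooled variance: sp² = (27r² + 471)/498
- SE ratio: k = √[sp²(1/28 + 1/472)] / √(r²/28 + 1/472)
- Error rate ≈ 2(1 − Φ(1.96k))

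At r = 1.5: sp² = (60.75 + 471)/498 = 1.068. The computed SE is √(1.068 × 0.03783) = 0.201, the true SE is √(0.08036 + 0.00212) = 0.287, and k = 0.70. The error rate is 2(1 − Φ(1.372)) = 17.0%.

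| r | k | Student, formula | Student, simulated | Welch, simulated |
|---|---|---|---|---|
| 0.7 | 1.37 | 0.7% | 0.7% | about 5% |
| 1.0 | 1.00 | 5.0% | 5.0% | about 5% |
| 1.25 | 0.82 | 10.8% | 10–11% | about 5% |
| 1.5 | 0.70 | 17.0% | 17% | about 5% |
| 2.0 | 0.55 | 28.0% | 28% | about 5% |

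Results at 25/475 and 30/470 are nearly the same (17.2% and 16.9% at r = 1.5).

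**Step 3: a wider adverse group.** If morbidities are counted, the group is larger. At r = 1.5, with assumed sizes of 100, 150 and 200 of 500, the same formula gives 12.1%, 9.3% and 7.0%.

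**Step 4: unequal spread caused by a shifted subset.** Let a fraction p of adverse cases be shifted by d SD and the rest be like the other group. The adverse mean then moves by pd and its SD becomes √(1 + p(1 − p)d²). The values of p and d are assumptions.

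| p | d | Mean shift | SD ratio | Student 95% CI coverage | Student rejects | Welch rejects |
|---|---|---|---|---|---|---|
| 20% | 2 | 0.4 | 1.28 | 88–89% | 52% | 34% |
| 20% | 3 | 0.6 | 1.56 | 81% | 75% | 48% |
| 30% | 2 | 0.6 | 1.36 | 86% | 79% | 61% |
| 30% | 3 | 0.9 | 1.70 | 78% | 94% | 78–79% |

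Welch's interval covers about 95% throughout. The means really differ here, so a rejection is correct; the fault is an interval that is too narrow.

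**Step 5: price of Welch under equal variances.** At a true difference of 0.55 SD, power is 78% for Welch and about 80% for Student.

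**The case against.** A reader might infer that the plan will declare false associations between Doppler measures and adverse outcome. The documents do not support that. The error rates in Step 2 need equal means with unequal spread. The reason the documents offer for unequal spread, a mix of causes, moves the mean as well (Step 4). In that setting Student's test overstates precision but does not invent a difference, and Welch's test rejects less often.

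Nor are these tests the plan's main evidence on Doppler. The article gives Doppler associations to logistic regression, which pools no variance, and the machine-learning model is untouched.

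Three further objections stand in part:

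- The split of 28 to 472 belongs to the deaths. The Introduction speaks of "adverse perinatal outcomes such as stillbirth, perinatal mortality, and other neonatal morbidities", and a group that includes morbidities would be larger. Step 3 shows a smaller error, though not none. The 25–30 is the only projection in the article.
- The article never says pooled or equal variance, and a fuller plan might settle the variance form. But the sentence names Student's test and fixes normality as the sole criterion. That is a stated choice and not only an omitted detail.
- No SD is given, so unequal spread is not shown. This is right, and it makes the harm conditional.

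A reader might also want Mann-Whitney replaced or a normality pre-test forbidden. Mann-Whitney is a conventional choice for non-normal data, and the article mentions no pre-test, so neither demand is made here.

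**Conclusion.** The point holds as a minor one. The article names a test that in its usual form assumes equal variances, for a comparison that is about 17:1 for deaths, and considers only normality. If the spreads differ, the nominal 5% error rate becomes about 10–11% to 28% at SD ratios of 1.25 to 2, and 0.7% at 0.7. With a larger adverse group of 100–200 women, it is about 12% down to 7% at a ratio of 1.5. If the spread comes from a shifted subset, the consequence is 95% interval coverage of about 78–88%.

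All of this rests on assumed SD ratios, a two-sided 5% level and the equal-variance reading of Student's test. It concerns the unadjusted comparisons only.

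**What to change.** In the Statistical analysis paragraph, replace Student's t-test with Welch's unequal-variance t-test, and report the mean difference with its Welch 95% confidence interval. The Mann-Whitney alternative can stay as written.

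The change is one sentence and needs no new data or women. It has two costs. Power falls by about 2–3 percentage points if the variances are equal. There are also fewer nominally significant results when the adverse group is more variable: 34% against 52% in the mildest scenario of Step 4, and 78–79% against 94% in the strongest. That second cost should be stated openly, because it is the price of intervals that cover at their stated rate.
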